## Abstract

**Background:**

Oral mucositis (OM) is the most frequent and debilitating acute side effect associated with head and neck cancer (HNC) treatment. When present, severe OM negatively impacts the quality of life of patients undergoing HNC treatment. Photobiomodulation is a well-consolidated and effective therapy for the treatment and prevention of severe OM, and is associated with a cost reduction of the cancer treatment. Although an increase in the quality of life and a reduction in the severity of OM are well described, there is no study on cost-effectiveness for this approach considering the quality of life as a primary outcome. In addition, little is known about the photobiomodulation effects on salivary inflammatory mediators. Thus, this study aimed to assess the cost-effectiveness of the photobiomodulation therapy for the prevention and control of severe OM and its influence on the salivary inflammatory mediators.

**Methods/design:**

This randomized, double-blind clinical trial will include 50 HNC patients undergoing radiotherapy or chemoradiotherapy. The participants will be randomized into two groups: intervention group (photobiomodulation) and control group (preventive oral care protocol). OM (clinical assessment), saliva (assessment of collected samples) and quality of life (Oral Health Impact Profile-14 and Patient-Reported Oral Mucositis Symptoms questionnaires) will be assessed at the 1st, 7th, 14th, 21st and 30th radiotherapy sessions. Oxidative stress and inflammatory cytokine levels will be measured in the saliva samples of all participants. The costs are identified, measured and evaluated considering the radiotherapy time interval. The incremental cost-effectiveness ratio will be estimated. The study will be conducted according to the Brazilian public health system perspective.

**Discussion:**

Photobiomodulation is an effective therapy that reduces the cost associated with OM treatment. However, little is known about its cost-effectiveness, mainly when quality of life is the effectiveness measure. Additionally, this therapy is not supported by the Brazilian public health system. Therefore, this study widens the knowledge about the safety of and strengthens evidence for the use of photobiomodulation therapy, providing information for public policy-makers and also for dental care professionals. This study is strongly encouraged due to its clinical relevance and the possibility of incorporating new technology into public health systems.

**Trial registration:**

Brazilian Registry of Clinical Trials—ReBEC, RBR-5h4y4n. Registered on 13 June 2017.

**Electronic supplementary material:**

The online version of this article (10.1186/s13063-019-3196-8) contains supplementary material, which is available to authorized users.

## Background

The association of chemotherapy (CT) and radiotherapy (RT) is the most frequent treatment approach for head and neck cancer (HNC) in cases of locally advanced disease [1]. Oral mucositis (OM) is the main side effect of RT and chemoradiation therapy (CRT) for HNC, its severity dependent on the number of RT sessions [2–6]. OM is an inflammatory reaction that can affect the entire oral cavity and gastrointestinal tract [7–10]. Intense pain, the need for nutritional supplementation, a higher number of clinical appointments and treatment interruption are common events associated with severe OM. These side effects may influence the survival rate and increase the costs of the HNC treatment [3, 5, 11–14].

CT and RT increase the levels of reactive oxygen species that may cause upregulation of transcription factors, such as NF-κB and STAT3 [4]. This increased level of transcription factors activates the production of inflammatory cytokines, such as matrix metalloproteinase, leading to tissue damage [4, 5, 15]. The use of photobiomodulation therapy (PBMT) has been encouraged and is described as effective therapy for OM treatment [16, 17]. Recent data showed that PBMT improves quality of life (QoL) and is effective in the control of OM, reducing the morbidity and costs associated with OM [16–24]. Oberoi et al. [18] concluded that PBMT reduced the number of severe OM episodes and pain associated with it. However, several protocols for PBMT have been described with differences in the laser wavelength, time of irradiation, frequency and energy used. They suggested that research should be conducted investigating the ideal parameters and clinical viability.

Although PBMT has been used for the treatment of CRT-induced OM, the mechanism of action of this therapy in the stressed oral cavity is not completely understood. Animal studies showed that the reduction of OM severity might be due to a reduction of COX-2 levels and the neutrophilic infiltrate in the wound; besides that, PBMT may also promote collagen organization, resulting in ulcer healing [25, 26]. Silva et al. [21] studied the effects of PBMT on the inflammatory mediators and oxidative stress of CT-induced OM. They showed that PBMT can enhance interleukin-10 levels, an anti-inflammatory cytokine that reduces the damage caused by neutrophils and macrophages, and suggested that interleukin-6 has an important role in OM. Salvador et al. [27] showed that PBMT can reduce the levels of interleukin-8 but did not find any differences in the antioxidant proteins in patients undergoing hematopoietic stem cell transplantation. Although these studies are about CT-induced OM, the initiation process of OM appears to be the same in CT-induced and RT-induced OM [4]; thus, the influence of PBMT on the levels of inflammatory cytokines may be similar.

Only a few studies have investigated the effects of PBMT on the inflammatory and oxidative stress proteins in CRT-induced OM. Oton-Leite et al. [28] showed that use of a red laser is associated with a reduction in inflammation and repair, evoking a less intense inflammatory response. In this specific study, patients were irradiated three times a week, and the authors suggested that additional studies with different protocols should be conducted to better understand the effects of PBMT in OM.

According to a study conducted in the USA in 2002, OM was associated with an incremental cost of US$1700–6000 in the HNC treatment, due to an increased resource use, hospital days, opioid use and other factors [13]. Nonzee et al. [11] reported an incremental cost of US$18,515 due to severe degrees of OM in lung cancer patients. The use of PBMT is associated with a reduction in the costs of severe OM. Bezinelli et al. [19] reported a reduction of 30% of the costs in patients undergoing hematopoietic stem cell transplantation who received PBMT to prevent OM.

Antunes et al. [29] conducted a cost-effectiveness study regarding the use of PBMT in the treatment of OM, taking into consideration the public health system perspective and the prevention of severe OM as the effectiveness measure. The authors concluded that the patients treated with PBMT presented an incremental cost of US$1689.00, when compared with the patients not exposed to PBMT; the incremental cost-effectiveness ratio was US$4961.37 per severe case of OM prevented. To our knowledge, there has not been a study that has evaluated the cost-effectiveness of PBMT for the control and treatment of OM based on patient-reported outcomes. This type of study may allow a comparison between the different technologies and drugs used for the treatment of OM.

Thus, the aim of this study is to assess the cost-effectiveness and molecular effects of PBMT in the treatment and prevention of severe OM. The hypothesis is that PBMT is more costly but more effective than conventional treatment of OM and that PBMT modulates the inflammatory and oxidative stress proteins. This study will contribute to a better understanding of the PBMT mechanism and may allow the laser technology to be consolidated and used in public health systems, providing a better QoL for patients undergoing HNC treatment.

## Methods/design

This study is a randomized, double-blind clinical trial that will be conducted in Araujo Jorge Cancer Hospital, Goiânia, Goiás, Brazil and the Faculty of Dentistry of the Federal University of Goiás, Goiânia, Goiás, Brazil. The study was approved by the Research Ethics Committee of the Federal University of Goiás and the Research Ethics Committee of the Araujo Jorge Cancer Hospital (Numbers 2.608.604/2018 and 2.131.323/2017, respectively). Moreover, the study was registered in the Brazilian Registry of Clinical Trials (RBR-5h4y4n). All participants who accepted to participate in the study signed a written informed consent form. Figure 1 shows the flowchart of the study and Fig. 2 presents the outcomes and time points according to recommendations for interventional trials (SPIRIT). A SPIRIT checklist is presented in Additional file 1.

**Fig. 1 Fig1:**
[figure not shown]
Flowchart of the study. RT radiotherapy

**Fig. 2 Fig2:**
[figure not shown]
Timeline of the study. *The allocation period and the baseline evaluation will be performed at the same appointment. RT radiotherapy

### Participants

The participants will be HNC patients of the Brazilian public health system—Brazilian Unified Health System (Sistema Único de Saúde (SUS))—who will be treated with RT, with or without CT, in Araujo Jorge Hospital, Goiânia, Goiás, Brazil. To estimate the study sample size, we used the OpenEpi online calculator (http://www.openepi.com). The 95% significance level (1 – α error type I), a study power of 80% (1 – β error type II) and a 1.0 ratio of unexposed/exposed were set as estimator parameters. Finally, we considered a prevalence of severe OM of 60% for the control group and 21% for the PBMT group (OR = 0.18) [18]. The calculated minimum sample size was 50 participants (25 per group) and an additional 10% was considered to compensate for possible loss to follow-up.

Individuals older than 18 years of age of both sexes will be included in the study, edentulous or not, with neoplastic lesions in the head and neck site (oral cavity, oropharynx, nasopharynx and advanced stage laryngeal tumors; T3 N1 or T3 N2 and T4 with any N status). All participants will be subjected to RT (with or without CT), with a minimum dose of 50 Gy, 2 Gy/day and five times per week, in the conventional scheme of RT. All patients will be treated with the Elekta Compact (Elekta AB, Stockholm, Sweden), a linear accelerator that generates photon radiation with fixed energy of 6 MV. Participants will be excluded if they present with an infection or salivary gland tumors, Sjögren’s syndrome, are submitted to palliative treatment or were previously treated with RT and/or CT in the head and neck area. Individuals diagnosed with lymphoma, melanoma or skin cancer will also be excluded.

In this hospital setting, every HNC patient who will be submitted to RT must be evaluated by the Dental Care Service to obtain authorization before starting the HNC treatment. On this occasion, the individuals will be invited to participate in the study. After acceptance, the principle researcher will obtain a signed written informed consent form from the participants. Participants will be excluded from the trial in cases of death, withdrawal or absence from five or more laser therapy sessions.

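### The 10% allowance for loss is missing from the only stated total: 50 is both the calculated minimum before loss and the number the abstract says will be included

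*Protocol article*

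**What the plan says.** The sample size is set in the Participants section of the protocol article. The error rates are given as "The 95% significance level (1 – α error type I), a study power of 80% (1 – β error type II". The effect is described thus: "we considered a prevalence of severe OM of 60% for the control group and 21% for the PBMT group (OR = 0.18". Allocation is equal ("a 1.0 ratio of unexposed/exposed were set as estimator parameters").

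The result and the loss allowance share one sentence: "The calculated minimum sample size was 50 participants (25 per group) and an additional 10% was considered to compensate for possible loss to follow-up". No total after the allowance follows, there or elsewhere in the text.

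The Methods/design part of the abstract gives the trial's size: "This randomized, double-blind clinical trial will include 50 HNC patients undergoing radiotherapy or chemoradiotherapy". It then says that these participants will be randomized into the two groups.

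The Participants section also lists reasons for removing participants after entry: death, withdrawal, or missing five or more laser sessions. Some loss is therefore expected by design.

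**The concern.** One place describes 50 as a floor to which an allowance is added. The other gives 50 as the size of the trial. Both can hold only if the word for inclusion in the abstract means patients left for analysis rather than patients enrolled, and the article does not say so.

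The sample size exists to support the 80% power claim. If recruitment stops at 50 and the anticipated loss occurs, the analysis falls below the number the authors themselves call the minimum. If recruitment goes on to 55 or 56, the abstract gives the wrong enrolment, and a later reader cannot tell whether the trial met its target.

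**Working it through.** **Inputs** (Participants section): control rate p1 = 0.60; PBMT rate p2 = 0.21; difference d = 0.39; power 80%, so z = 0.84162; allocation 1:1; loss 10%. The article does not state sidedness. I assume two-sided 5%, so z = 1.95996.

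Mean rate p̄ = (0.60 + 0.21)/2 = 0.405.
Pooled variance term: 2 × 0.405 × 0.595 = 0.48195.
Separate variance term: 0.60 × 0.40 + 0.21 × 0.79 = 0.4059.
d² = 0.1521.

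**Step 1. Reproduce the stated 25 per group.**

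- Pooled variance for both terms: n = (1.95996 + 0.84162)² × 0.48195 / 0.1521 = 7.8489 × 0.48195 / 0.1521 = 24.87, so 25 per group and 50 in total. This matches the article exactly.
- Fleiss formula without continuity correction: n = (1.95996 × √0.48195 + 0.84162 × √0.4059)² / 0.1521 = 23.66, so 24 per group and 48 in total, within two patients of the stated figure.

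The odds ratio also agrees: (0.21/0.79)/(0.60/0.40) = 0.177, stated as 0.18.

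**Step 2. Is the 10% already inside the 50?** If it were, the calculation before loss would have given 50 × 0.9 = 45, or 22.5 per group. The two formulas give 24.87 and 23.66. The wording agrees, since it calls 50 the calculated minimum and the 10% additional. So 50 is the figure before loss.

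**Step 3. Enrolment with the allowance.**

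- Adding 10%: 50 × 1.10 = 55. A 10% loss then leaves 49.5.
- Dividing by the retained fraction: 50/0.9 = 55.6, so 56 (28 per group). A 10% loss then leaves 50.4.

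**Step 4. Power if 50 are enrolled and 10% are lost.** 50 × 0.9 = 45 evaluable, 22.5 per group.

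- Pooled formula: power = Φ(d√n/√0.48195 − 1.95996). At n = 22.5 this is Φ(2.665 − 1.960) = Φ(0.705) = 76.0%.
- Fleiss: power = Φ((d − 1.95996 × √(0.48195/n)) / √(0.4059/n)). At n = 22.5 this is Φ((0.39 − 0.28685)/0.13431) = Φ(0.768) = 77.9%.

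| Evaluable | Pooled formula | Fleiss, no correction |
|---|---|---|
| 50 (25 per group) | 80.2% | 82.3% |
| 45 (22.5 per group) | 76.0% | 77.9% |

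As a cross-check, exact enumeration of the uncorrected chi-square test with 45 patients gives 79.0% (23 control, 22 PBMT) or 77.8% (22 control, 23 PBMT), against 84.8% at 25 per group. These also fall below 80%.

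**The case against.** The strongest reply is that the plan does provide for loss. The Participants section says so, and the contrary evidence is one sentence of a condensed abstract. The 50 there may be the evaluable minimum, with about 55 recruited. The flowchart (Fig. 1) is not shown in the text available and might carry a recruitment figure. The Participants section also gives no total after the allowance, so strictly there are not two rival targets. There is a minimum plus an addition in one place, and a total without the addition in the other.

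Much of this stands. It rules out a flat statement that the trial will not have its stated power, which a reader might infer from the abstract. That conclusion needs the 50 to be the number enrolled, and the documents do not settle the point. The reply does not remove the inconsistency. The abstract goes on to randomize the 50, which reads most naturally as enrolment. If evaluable patients were meant, the recruitment target appears nowhere in the text, and a figure of 55 or 56 in the flowchart would still disagree with the abstract.

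It is also fair that the effect is small. Uncertainty in the assumed 60% and 21% could plausibly matter more than a few points of power.

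**Conclusion.** The inconsistency is established: 50 is the size before loss, an additional 10% is announced, and the only total in the text leaves it out. The consequence is conditional.

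- If 50 is the number enrolled, the planned 10% loss leaves 45 and power of about 76% to 78%, roughly 2 to 4 points below the stated 80%.
- If 50 is the number evaluable, power is kept at 80% to 82% and the abstract misstates enrolment.

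The figures assume a two-sided 5% level, the stated 60% and 21%, and a two-proportion comparison without continuity correction, which is the calculation that reproduces 25 per group.

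A reader might go further and infer that the 25 per group is itself too small, because a continuity correction or an exact test would ask for more, because the exclusion rule could remove more than 10%, or because simple randomization need not give equal groups. The documents do not support building these into the point. The calculation states no correction, an uncorrected formula is a legitimate choice, no exact test is named, and 10% is the only loss rate given. Unequal groups under simple randomization are a separate, minor matter that does not bear on the missing allowance.

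**What to change.** State one enrolment target, and use it in both the abstract and the Participants section.

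- If the allowance was meant to be recruited, write 55 (adding 10% to 50) or 56 (50/0.9), whichever the authors used, and say that 50 is the number needed for analysis.
- If 50 is the enrolment, keep it and restate power as about 76% to 78% with 45 evaluable after 10% loss, naming the two-proportion calculation and its two-sided 5% level. Tie the restated power to that calculation rather than to a named test: the statistical analysis section assigns the Pearson chi-square test to participant characteristics and the Mann–Whitney test to mucositis severity.

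The first option costs a corrected number in the abstract, plus five or six more patients if recruitment had been planned to stop at 50. The second costs one sentence and a slightly less favourable power figure.

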### Study groups

#### Group 1: photobiomodulation therapy

The participants in this group will be submitted to laser therapy five times a week, during the RT. The PBMT protocol will begin in the first RT session, be conducted before each RT session and continue until the end of the treatment. Since the RT sessions will be scheduled in a specific hour, it will be possible to control participant appointments. If severe OM develops at the end of the RT, the patient will receive additional sessions.

The Twin Flex Evolution Laser (MMOptics, São Paulo, Brazil) will be used at a wavelength of 660 nm (red laser), 25 mW of power, in continuous mode, with punctual and perpendicular application in contact with the mucosa. The transferred energy will be 6.2 J/cm^2^ for 10 s on a spot area of 0.04 cm^2^, and thus energy of approximately 0.25 J will be deposited at each point. Before each session, the tip of the laser will be disinfected with a solution of 70% alcohol and wrapped in a plastic film. The laser beam will not be irradiated in a malignant lesion smaller than 1 cm if observed, or near a surgical site.

Specific anatomical regions be considered for the PBMT: right and left buccal mucosa (10 points on each side), upper and lower labial mucosa (four points on each lip), hard palate (three points), lateral surface of the tongue (10 points on each side), soft palate (three points), dorsal tongue (three points), floor of the mouth (two points) and labial commissure (one point on each side). This protocol is based on a previous study by Oton-Leite et al. [30].

The participants will also be submitted to a dental care protocol that consists of elimination of the infection focus, a fluoride rinse, a chlorhexidine 0.12% rinse three times a day diluted in water in a 1:1 proportion, recommendation to drink at least 1.5 L of water per day and the maintenance of good oral hygiene. If the presence of OM is observed, an oral ointment with hydrocortisone 5 mg, neomycin 5 mg, troxerutin 20 mg, ascorbic acid 0.5 mg and benzocaine 2 mg will be prescribed (Gingilone; Farmasa, São Paulo, Brazil).

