#### Oral mucositis evaluation

An assessor who is blinded to the treatment will conduct the OM evaluation. The researcher responsible for the PBMT will take intraoral pictures and save them on a hard disk for later evaluation. The evaluation will be in the first appointment and after the 7th, 14th, 21st and 30th RT sessions. The photographs will be taken using a T3i camera, with a circular flash (MR-14EX II) and a lens of Ef-s 18–55 mm F/3.5–5.6 (Canon, Tokyo, Japan). Pictures of the upper and lower labial mucosa, buccal mucosa, hard and soft palate, lateral surface of the tongue and floor of mouth will be acquired.

For the OM classification, the World Health Organization (WHO) [31] and the National Cancer Institute (NCI) [32] classifications will be used.

According to the WHO scale, the OM is classified as: 0, no signs or symptoms; 1, oral soreness and erythema; 2, erythema, ulcer, both solid and liquid diets tolerated; 3, ulcers and liquid diet only; 4, oral alimentation is impossible. The NCI scale is a graduated scale as follows: 0, no visible alterations; 1, presence of erythema; 2, noncontiguous ulcers up to 1.5 cm in diameter; 3, contiguous ulcers larger than 1.5 cm in diameter; 4, ulcers showing necrosis and bleeding. In this study, OM will be considered severe when classified with grades 3 or 4 according to the NCI and/or WHO scales.

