#### Quality of life

The translated, adapted and validated Brazilian version [33] of the Oral Health Impact Profile, in its simplified form (OHIP-14) [34], will be used to assess the oral health-related quality of the participants. This questionnaire contains 14 questions, divided into seven subscales: functional limitation, physical pain, physiological discomfort, physical disability, physiological disability, social disability and handicap. The questions will be answered on a 5-point Likert scale, the responses will be summarized and the final score will be calculated.

The translated version of the Patient-Reported Oral Mucositis Symptoms (PROMS) scale will also be used to assess the OM effects reported by the patient [35]. This scale was originally used to assess OM due to CT; however, its use in patients undergoing RT is also feasible [36, 37]. The scale contains 10 questions, which are answered on a 10-cm uninterrupted visual analog scale. The participant will be asked to indicate the score for each item. The sum of the 10 items will be used as the PROMS score.

These instruments will be applied during the first appointment and after the 7th, 14th, 21st and 30th RT sessions based on previous studies [23, 38] that also evaluated the QoL weekly. As reported earlier, the OM evaluation will occur at the same time points. The questionnaires will be applied before the PBMT session and if the participant is not able to answer, a calibrated healthcare professional will provide help.

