#### Saliva collection and analysis

The collection of saliva will be performed before initiating the HNC treatment and after the 7th, 14th, 21st and 30th RT sessions, based on the method of Oton-Leite et al. [28] and Navazesh [39]. The participants will be instructed not to eat or drink 1 h before the collection of saliva.

The collection of unstimulated saliva will be performed in an artificial light environment, with the participants sitting with their eyes open, with their head slightly tilted down, without talking, opening their mouth or swallowing the saliva during the time of collection. Initially, the participants will be instructed to wash their mouth with water and swallow any saliva in their mouth. The participants will then be instructed not to swallow for a period of 5 min in order to accumulate saliva. This accumulated saliva will be deposited in a sterile Falcon-type millimeter tube.

The sample will be centrifuged for 15 min at 4500 rpm. The samples will then be transferred to another tube and diluted (1:1) in PBS solution (0.4 mM NaCl and 10 mM NaPO_4_) containing protease inhibitors (0.1 mM phenylmethylsulfonyl fluoride, 0.1 mM benzethonium chloride, 10 mM EDTA and 0.01 mg/ml aprotinin A) and 0.05% Tween-20. The solution will be homogenized, distributed in aliquots of approximately 2 ml and frozen at − 80 °C. The concentrations of inflammatory cytokines, nitrite and total proteins will be assessed in each saliva sample.

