### Cost-effectiveness analysis

The incremental cost-effectiveness ratio (ICER) will be calculated considering the incidence of severe degrees of OM as the measure of effectiveness for the PBMT and control groups. We will also measure the effectiveness based on patient-reported outcomes (including QoL measures). A decision tree-type diagram will be created to represent all clinically relevant events.

The ICER will be calculated to determine the cost-effectiveness of PBMT. The ICER will be calculated by dividing the cost difference (Cost2 – Cost1) by the difference between the frequency of severe OM in both groups. The ICER will represent the incremental cost to avoid one case of severe OM using PBMT.

Additionally, another ICER will be calculated by dividing the cost difference (Cost2 – Cost1) by the difference between the QoL in both groups. The ICER represents the incremental cost to avoid the loss of 1 point on the QoL measure, assessed using the difference between the last evaluation (30th RT) and the baseline (0 RT). Two different ICERs will be calculated considering the scores of each instrument (OHIP-14 and PROMS). The following formula summarizes the ICER analysis.$$ \mathrm{ICER}=\left(\mathrm{Cost}2-\mathrm{Cost}1\right)/\left(\mathrm{QoL}2-\mathrm{QoL}1\right) $$

Univariate sensitivity analysis will be performed to assess the uncertainty in the parameters associated with PBMT.

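### The 50 Gy eligibility floor (25 sessions) does not fit a final assessment and a QoL ICER endpoint fixed at the 30th RT session

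*Protocol article*

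**What the plan says.** Under Participants, eligibility is set by dose and fractionation: "with a minimum dose of 50 Gy, 2 Gy/day and five times per week". No upper dose and no minimum number of sessions is stated.

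The assessment schedule is set by session number. For OM: "The evaluation will be in the first appointment and after the 7th, 14th, 21st and 30th RT sessions". The Quality of life section gives the same time points for OHIP-14 and PROMS, and the Saliva collection section schedules samples "before initiating the HNC treatment and after the 7th, 14th, 21st and 30th RT sessions". The abstract also ends the schedule at session 30.

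Under Cost-effectiveness analysis, the QoL effect in the incremental cost-effectiveness ratio (ICER) is "assessed using the difference between the last evaluation (30th RT) and the baseline (0 RT"). One such ratio is planned for each instrument.

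Treatment is tied to the end of RT instead. For Group 1, photobiomodulation will "be conducted before each RT session and continue until the end of the treatment", and "If severe OM develops at the end of the RT, the patient will receive additional sessions". The abstract sets the RT interval as the cost horizon.

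**The concern.** Eligibility and endpoint are both stated in the article, and they do not match. Some patients whom the protocol admits will finish RT before the visit on which two of the three ICERs depend. This is more than an unstated rule for handling missing data. No visit is scheduled between session 21 and session 30, so the data would never be collected and no later analysis plan could restore them.

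The abstract and the Discussion present cost-effectiveness based on patient-reported outcomes as the gap that this study fills, so the QoL change score is a central endpoint. The Background also says that OM severity depends on the number of RT sessions. The patients without a final value would thus be a group defined by a factor related to the outcome. In the same patients, severe OM that first appears after session 21 would have no blinded photographic assessment.

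**Working it through.** **Inputs.** From Participants: minimum dose 50 Gy, 2 Gy per session, five sessions a week, 25 patients per group. From the OM, QoL and saliva sections: assessments at baseline and after sessions 7, 14, 21 and 30. From Cost-effectiveness analysis: QoL effect = session 30 minus baseline.

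**The plan's own figure.** The sample size is not in dispute. For 60% versus 21% severe OM, with two-sided α of 0.05 (two-sided is assumed), 80% power, 1:1 allocation and no continuity correction, the formula gives 24 per arm, or 48 in total, against the stated 50. Power at 25 per arm is 82.3%. This calculation concerns severe OM and does not size the QoL comparison.

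**Sessions per course.** Sessions = total dose / 2 Gy. The minimum course is 50/2 = 25 sessions. Session 30 needs 30 × 2 = 60 Gy.

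| Total dose (Gy) | Sessions | Reaches session 30? | Last scheduled assessment | Sessions left after it |
|---|---|---|---|---|
| 50 | 25 | no | 21 | 4 |
| 52 | 26 | no | 21 | 5 |
| 54 | 27 | no | 21 | 6 |
| 56 | 28 | no | 21 | 7 |
| 58 | 29 | no | 21 | 8 |
| 60 | 30 | yes | 30 | 0 |
| 64 | 32 | yes | 30 | 2 |
| 66 | 33 | yes | 30 | 3 |
| 70 | 35 | yes | 30 | 5 |

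The doses above 60 Gy are illustrative, because the article gives no maximum. Only a 60 Gy course has its last assessment at the end of RT.

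**What a 25- to 29-session patient contributes.**
- OM: values at baseline and sessions 7, 14 and 21, but none later.
- OHIP-14 and PROMS: the same four time points, but no change score as defined.
- Saliva: the same four time points, but no final sample.

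**Size.** The share f of patients on 50 to 58 Gy is not given, so it is an assumption here. The loss from each QoL ratio is 50 × f. If the loss is spread evenly over the arms and the spread of scores is unchanged, the standard error of the difference in mean change grows by 1/√(1 − f).

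| f (assumed) | Lost of 50 | Standard error multiplied by |
|---|---|---|
| 0% | 0 | 1.00 |
| 10% | 5 | 1.05 |
| 20% | 10 | 1.12 |
| 30% | 15 | 1.20 |

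The planned 10% allowance for loss to follow-up would offset roughly the first 10% in numbers, if it were not also needed for true losses.

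**The case against.** **The floor may rarely apply.** 50 Gy is a minimum, and patients on palliative treatment or with earlier head and neck RT or CT are excluded. Few or no patients may fall below 60 Gy. This stands as a limit on the size of the problem. It does not remove the mismatch, because the protocol admits these patients and gives no rule for them.

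**The article is condensed.** The timeline figure is not shown, and handling of a missing final visit is commonly left to an analysis plan. But the text names session 30 consistently in the abstract, the OM, QoL and saliva sections and the ICER definition. A last evaluation might be read flexibly if the parenthesis in the ICER definition did not fix it at session 30.

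**Stronger readings that a reader might infer, and that the document does not support:**
- *Short-course patients have no endpoint.* They still contribute severe-OM data at sessions 7, 14 and 21. The sample size rests on severe OM, and so does the first ICER described.
- *Late severe OM is never counted.* Severe episodes, hospitalizations, opioid use and parenteral nutrition are costed from hospital records, so a late case can still enter the cost side. What is absent is a scheduled blinded photographic assessment.
- *The result is biased toward one arm.* Nothing links RT dose to the randomized arm.
- *These patients drop out of every Friedman test.* That would follow from complete-case handling over all five time points, which the article does not state.
- *Stopping at session 30 is also an error for longer courses.* A fixed session compares patients at the same cumulative dose of 60 Gy and contradicts no statement in the article. The provision for severe OM at the end of RT implies some clinical look then. An added assessment would be an improvement, not a correction.

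**Conclusion.** The concern holds in a limited form. The eligibility floor of 25 sessions and the final assessment at session 30 cannot both be followed for courses of 50 to 58 Gy. As written, these patients have no OHIP-14 or PROMS change score and no final OM or saliva value, and their last 4 to 8 sessions go without a scheduled assessment. This follows from the article's figures alone and assumes only that the fractionation is kept.

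The impact is uncertain because the dose distribution is not given. It ranges from nothing, if all courses reach 60 Gy, to 5 of 50 patients lost from both QoL ratios for each 10% on shorter courses. The expected harm is lost precision and incomplete ascertainment in both arms. The change should be made, because the endpoint is central and the remedy is cheap.

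**What to change.** Reconcile the sections by defining the final OM, QoL and saliva evaluation as *the 30th RT session, or the last RT session if earlier*. Use that definition in the OHIP-14 and PROMS ratios in place of the 30th session. No radiotherapy dose or treatment rule needs to change.

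**Cost.** The change is one of wording, plus the usual assessment at a session that the patient already attends: both arms have laser or sham appointments, and the researcher giving the laser therapy already takes the photographs. The timing of the final visit will vary a little, between sessions 25 and 30. Recruitment and treatment began in August 2017, so final values cannot be recovered for short-course patients who have already finished RT. Their number should be reported by arm, and the rule should be fixed before any unblinded analysis.

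**Optional improvement.** For courses longer than 30 sessions, repeat the photographs and questionnaires at the last attended RT session and count the photographs towards severe-OM incidence. Costs cover the whole RT interval while scheduled effects stop at session 30, and this would bring the two closer for the severe-OM ratio. The QoL ratios would still end at session 30 unless their definition were also extended. The cost is one more set of photographs and questionnaires per such patient.
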